## Abstract

**Background:**

The optimal management for severe sprains (Grades II and III) of the lateral ligament complex of the ankle is unclear. The aims of this randomised controlled trial are to estimate (1) the clinical effectiveness of three methods of providing mechanical support to the ankle (below knee cast, Aircast^® ^brace and Bledsoe^® ^boot) in comparison to Tubigrip^®^, and (2) to compare the cost of each strategy, including subsequent health care costs.

**Methods/design:**

Six hundred and fifty people with a diagnosis of severe sprain are being identified through emergency departments. The study has been designed to complement routine practice in the emergency setting. Outcomes are recovery of mobility (primary outcome) and usual activity, residual symptoms and need for further medical, rehabilitation or surgical treatment. Parallel economic and qualitative studies are being conducted to aid interpretation of the results and to evaluate the cost-effectiveness of the interventions.

**Discussion:**

This paper highlights the design, methods and operational aspects of a clinical trial of acute injury management in the emergency department.

## Background

Sprains of the lateral ligaments of the ankle joint account for between 3 and 5% of all emergency department (ED) attendances in the UK [1], with approximately 5600 injuries each day [2]. The injury is painful and incapacitating, and, for all but the most minor injuries, weight bearing is difficult to tolerate. Activities of daily living can be significantly compromised in the first few weeks, and although acute symptoms resolve, persistent symptoms are reported to occur in between 30 to 50% of people [3-6]. Persistent symptoms include recurrent sprains, instability, swelling, unsightly appearance and pain. Crichton has developed a classification of severity of ankle injuries [7].

• GRADE I – the ligament is stretched but not torn and the anterior talofibular ligament is usually involved. The anterior draw test is negative.

• GRADE II – the ligaments are partially torn; laxity may be present and there is moderate swelling.

• GRADE III – complete rupture of the ligament resulting in joint instability. The anterior draw test is positive.

The focus of this trial is Grade II and III sprains (referred to as severe sprains from this point). Severe sprains have poorer prognosis, and necessitate more intensive management than Grade I sprains (minor sprains). Minor sprains are considered to be self-limiting and require minimal treatment.

Recent systematic reviews have highlighted the lack of high quality evidence to support clinicians in managing severe sprains [2,7]. There are few reliable studies describing long-term outcome. Most trials required x-ray evidence of talar tilt or an arthrogram for inclusion and are, therefore, not generalisable to clinical practice in the ED. Current practice ranges from no intervention, physiotherapy, and different types of mechanical support to surgical repair of the ligaments. A recent UK survey of 83 EDs demonstrated the most popular treatments were ice, elevation, Tubigrip^® ^support stocking and exercise, each of which was reported as being used in most cases by over 70% of respondents [8]. In addition, over half of responding departments reported that crutches, early weight bearing, and non-steroidal anti-inflammatory drugs were used in most cases. Follow up was used only in selected cases.

Practice has been gradually changing from immobilisation of the injured joint to early mobilisation. To aid mobilisation the use of mechanical supports has been suggested. These supports vary in the amount of ankle movement they allow, but all encourage ankle flexion/extension and aim to minimise inversion/eversion that theoretically reduces the risk of further ligament injury. Movement is also proposed as a way of retraining the ankle proprioception which may reduce recurrent injury rate [9]. Other hypothesised benefits of mechanical supports are early restoration of functional mobility, rapid return to usual activities, reduction of pain because the joint is stabilised and protected, and improved quality of life. However, there is also the possibility of discomfort and inconvenience owing to restriction of joint range, and delayed healing, skin and circulatory problems.

The present study has two aims

1. To estimate the clinical effectiveness of three different methods of mechanical support (below knee cast, Aircast^® ^ankle support and Bledsoe^® ^boot) in comparison to Tubigrip^® ^in

a. The recovery of mobility (primary outcome)

b. The recovery of usual occupation

c. Avoidance of residual symptoms including recurrent instability, lasting limitation of physical activity, and need for further medical, rehabilitation or surgical treatment.

2. To measure the cost of each strategy, including treatment and subsequent health care costs.

The NHS National Co-ordinating Centre for Health Technology Assessment has guided the selection of treatments. Tubigrip^® ^has been chosen as the reference treatment because it is the cheapest and one of the most commonly used [10]. The Bledsoe^® ^boot is lightweight and incorporates a novel design to promote ease of walking. However it is considerably more expensive, and it's clinical and cost effectiveness is yet to be proven. The below knee cast is Scotch^® ^Cast is commonly used for casting in the NHS [9]. There is a range of lightweight mechanical supports available, and we have selected the Aircast^® ^Brace.

## Methods

This pragmatic randomised controlled trial is being run in 6 trusts (covering eight hospitals) across the UK. The trusts are: Birmingham Heartlands and Solihull NHS Trust, North Bristol NHS Trust, Oxford Radcliffe Hospitals NHS Trust, South Warwickshire General Hospitals NHS Trust, University Hospitals Coventry and Warwickshire NHS Trust and the Worcestershire Acute Hospitals NHS Trust. Figure 1 provides an overview of the trial method and patient journey. Multi-centre Research Ethics Committee approval has been awarded by the Northern and Yorkshire Regional Office and local ethical and research governance approvals have been obtained. Informed consent to participate in the trial and allowing researchers to access hospital records is obtained from all participants.

**Figure 1 F1:**
[figure not shown]
Study design

### Study population

The target population is people attending the ED with a severe sprain of the lateral ligament complex of the ankle.

### Inclusion criteria

People who attend with sprain of the ankle who are unable to weight bear, aged 16 years and older, and give informed consent. Weight bearing is used as a proxy for severe sprains as clinical grading is not possible in the acute phase [7]. Flake fractures (<=2 mm) of the lateral malleolus are included as they are normally treated as soft tissue injuries [11].

### Exclusion criteria

Age less than 16 years old, ankle or other fracture sustained in addition to the sprain (such as to the wrist, head etc). An x-ray is used to exclude fracture where this is clinically indicated and as guided by the Ottawa guidelines [12]. People who can weight bear and those with fractures are ineligible for the trial, and are managed in accordance with normal local practices. Age is used as an exclusion criterion because of the complications involved in the management of epiphyseal injuries (growth plate injuries). Growth plate injuries would not normally be managed using the treatments being tested [13].

Patients are also excluded if they have a contra-indication to any of the four arms of the trial. This is most likely to occur if a patient has a DVT, high risk of DVT or other circulatory disturbance. Other contra-indications include poor skin viability preventing splinting or casting. The decision to exclude on these criteria is made by the attending clinician.

### The process of identifying participants

A standard approach to identifying potential participants has been instituted across all participating centres. The approach was designed in consultation with the departments to dovetail with current procedures, and eradicate duplication of clinical and research data collection. The attending clinician (nurse practitioner, physiotherapist or doctor) assesses weight-bearing status. These data are recorded on a form that includes details of the remainder of the clinical examination, including if indicated, x-ray results. At this stage, people able to weight bear are excluded.

The attending clinician gives a brief explanation of the trial, an information pack, and arranges an appointment at a follow-up clinic two to three days later. Delay is an accepted practice in the application of mechanical supports, allowing for the resolution of acute swelling. It also filters out patients in whom the diagnosis of severe sprain at initial contact was incorrect, and gives participants sufficient time to consider whether they wish to participate in the trial. A physiotherapist who staffs the follow-up clinic is responsible for checking eligibility and providing a further opportunity for patients to ask questions. If appropriate, the physiotherapist recruits the patients, contacts the randomisation centre, and arranges application of the treatments. Reasons for declining to participate in the trial are recorded.

### Assessing the generalisability of the results

Data on all ankle sprains attending the participating EDs during the recruitment period are collected using a standardised proforma. A copy of this proforma, which is entered into the medical record, is anonymised and passed to the research team. It provides descriptive data on the injury pattern, occupation, age, and sex of patients, including those who are ineligible or decline trial participation at various time points. Completed proformas are audited against ED attendance records to check whether attending clinicians have referred appropriate patients to the follow-up trial clinics. This allows clinicians who are unfamiliar with the trial to be identified and approached individually to be briefed on trial procedures.

### Treatment allocation

Randomisation is stratified by centre and provided via a phone-in service, which utilises a computer generated random allocation. Allocation concealment, which shields people who enter patients into a trial from knowing future allocations, is thereby ensured. The randomisation service is independently administered and quality controlled by the Birmingham Cancer Trials Unit.

### Treatment protocol

The mechanical supports are fitted to each individual by a trained health professional (physiotherapist, nurse or plaster technician) in the follow-up clinic, to ensure comfort and correct fit. Participants are provided with standardised written and verbal instructions including when to remove the support, encouragement of normal walking with limits of tolerance, simple exercise advice, what to do in the event of experiencing difficulties with the support, and washing instructions. The protocols for duration of support, weight-bearing status, and activity have been determined by the manufacturers recommendations and the results of a national survey of practice completed in the planning phase of the trial [8]. Treatments are applied within three days of the injury, and within an hour of randomisation.

### Other treatments

All other treatments are standardised and include the provision of crutches, advice to elevate and pain relieving medications if needed. Withdrawal of the latter treatments would be inappropriate as they constitute normal and accepted care. Physiotherapy is not provided as part of the trial treatment protocol, and is not part of routine care provided in the participating centres [9]. If the participant receives these types of treatment in addition to the trial protocol, this is recorded as an outcome.

### Baseline and outcome measures

Clinical status is measured at baseline, 4 weeks, 12 weeks and 9 months. The baseline assessment also includes date of birth, sex, body mass index, ethnicity, an assessment of pre-injury abilities including usual levels of mobility, engagement in sporting activity, usual occupation and employment (including hours worked and type of work undertaken) and completion of the baseline version of the outcome questionnaires.

The selection of outcome measures is based on a systematic review completed during the preparatory stage [14], and are shown in Table 1. There is a paucity of information on the psychometric properties of self-completed questionnaires for ankle conditions. The Foot and Ankle Outcome Score (FAOS) is a questionnaire that ascertains functional limitations (including mobility) and the severity of other symptoms after ligament sprains, and has evidence of validity and reliability [10]. Previous versions have been validated against objective tests of ankle function [15]. The Functional Limitations Profile (FLP) is the British version [16] of the Sickness Impact Profile [17]. We are using the FLP occupation and mobility sub-scales to provide more detailed information on the impact of the injuries and treatments including adaptations that occur after the injury. The FLP has not been used in studies of ankle injuries previously. Health related quality of life will be measured using the SF-12 version 1 and EQ-5D [18]. Return to normal occupation and leisure activities will be recorded as the date that people return to work and normal activities. Patients are asked to make a record of significant dates on a calendar to aid recall. The effectiveness of these calendars is being tested in a separate study.

**Table 1 T1:** Outcome measures

**Outcome**	**Outcome measure**
Functional limitations and severity of symptoms after ligament sprains	Foot and Ankle Outcome Score (FAOS)
Impact of injuries and treatments including adaptations that occur after injury	Functional Limitations Profile (FLP) occupation and mobility sub scales
Health related quality of life	Short Form 12 version 1 (SF-12 v1)
Health related quality of life	EuroQol (EQ-5D)
Health economics	Resource Use Questionnaire
Return to normal occupation and leisure activities	Date of return to work and normal activities recorded on a trial calendar

### Timing of follow-up

The mechanical supports are likely to have maximal impact and benefit during the first three months of recovery, and this time period is defined as the primary time point. We anticipate that some participants will still be wearing the mechanical support at 4 weeks. The natural time course of recovery of ankle sprains is for functional limitations to stabilise between 3 and 9 months and it is expected that the difference between treatments will narrow in the longer term as the majority of people will recover [3,5,6]. Participants will be followed to 9 months to ensure that there are no longer-term complications from injury or their treatments.

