### Sample size

Although there was a paucity of published data available to inform the sample size estimate at the outset of the trial, the preliminary phase of the study has enabled us to make a more accurate estimation of the sample size required. The presented estimate is based on a standard sample size calculation for a two-sample t-test with equal variances and a significance level of 0.05, using the variance estimated from an ANOVA of the 4-week data (n = 100). The minimal clinically important difference is set at 10 percent, which represents a small to moderate effect size. A target of 600–650 participants will allow us to detect clinically important outcomes at 4 and 12 weeks. We are powered >90% to detect differences of 10 percent in the primary outcomes, and have sufficient power to detect differences in a range of secondary outcomes at 80% power. To account for the possibility of loss to follow-up, the estimate includes an inflation of 20%. However, the trial should be able to report whether any of the treatments have a sustained negative effect on outcome at 9 months. We are taking a pragmatic approach to estimating the sample size, and the Data Monitoring Committee are reviewing assumptions underlying the calculation at 6-monthly intervals.

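### The primary time point is defined as a three-month period that contains both the 4-week and the 12-week assessment, and nothing says which of them decides the trial

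*Protocol article*

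**What the plan says.** All references are to the protocol article.

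- **Timing of follow-up** defines the primary time as a span: the supports are expected to do most "during the first three months of recovery, and this time period is defined as the primary time point". The next sentence adds: "We anticipate that some participants will still be wearing the mechanical support at 4 weeks". The section then expects functional limitations to stabilise between 3 and 9 months and treatment differences to narrow in the longer term.
- **Baseline and outcome measures** gives the schedule: "Clinical status is measured at baseline, 4 weeks, 12 weeks and 9 months".
- **Sample size** serves two visits: "A target of 600–650 participants will allow us to detect clinically important outcomes at 4 and 12 weeks". Its variance comes from 4-week data on 100 participants.
- **Data analyses** compares each of the three supports with Tubigrip first, and compares with each other only those found more effective. Random-effect models are planned for centres and repeat assessments, in order to study components of variation. The section regards multiplicity as a minor issue because the analyses are pre-specified.

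**The concern.** A primary time point should identify one assessment, or one summary of several. This definition identifies a window with two post-baseline visits in it. No rule applies if a support beats Tubigrip at one visit and not at the other, and either result could be presented as primary.

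The visits are not interchangeable. At 4 weeks some participants are expected still to be wearing the device, so the score may partly reflect the device being on. By 12 weeks it should be closer to a measure of recovery.

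The choice also carries forward. A support enters the support-versus-support comparisons only if it is found better than Tubigrip, so the visit chosen decides which of those comparisons take place.

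Pre-specification is the reason given for setting multiplicity aside, but for time of assessment the specification is incomplete.

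**Working it through.** **1. Does any section resolve the ambiguity?**

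- Timing of follow-up: a period, not a visit.
- Baseline and outcome measures: 4 and 12 weeks lie inside the period; 9 months lies outside.
- Sample size: the 4- and 12-week visits are named together, with neither first. The plural in "We are powered >90% to detect differences of 10 percent in the primary outcomes" refers to outcomes, not visits, and settles nothing about time.
- Data analyses: no contrast over the period, no order, no alpha split.
- Economic analysis: mentions 12 weeks and 9 months, but only for resource use and outcomes in the economic comparison.

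No section picks one assessment.

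**2. The plan's own figure.** The target of 600–650 cannot be reproduced, because no standard deviation is given. It can only be solved backwards. Assume four equal arms, a two-sided 0.05 level, 20% loss, and 10 percent read as 10 points on a 0–100 scale.

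- Evaluable per arm: 600 × 0.8 / 4 = 120; 650 × 0.8 / 4 = 130.
- Largest SD giving 90% power: 10 / [(1.960 + 1.282) × √(2/n)] = 23.9 for n = 120 and 24.9 for n = 130.

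This is plausible but cannot be verified. It rests on a 4-week variance; the article gives no 12-week variance.

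**3. Error if either visit may be the headline.** Inputs:

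- Level: 0.05 per comparison (Sample size). Sidedness is not stated; two-sided is assumed.
- Visits: two, at 4 and 12 weeks.
- Correlation ρ between the two test statistics: not in the documents, assumed.

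Under no true effect, with Z₄ and Z₁₂ bivariate standard normal with correlation ρ:

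P(either significant) = 1 − P(|Z₄| < 1.96 and |Z₁₂| < 1.96).

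At ρ = 0 this is 1 − 0.95² = 0.0975. Otherwise it comes from the bivariate normal distribution:

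| ρ | Either visit significant | Either visit significant in the support's favour |
|---|---|---|
| 0 | 9.75% | 4.94% |
| 0.3 | 9.51% | 4.76% |
| 0.5 | 9.07% | 4.54% |
| 0.7 | 8.35% | 4.17% |
| 0.9 | 7.04% | 3.52% |

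With one named visit the columns would read 5% and 2.5%. The last column matters because only a result in the support's favour opens the later comparisons.

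**4. Do the remedies restore the level?** One named visit, or one contrast over both, gives 5%. So does a fixed order in which the second visit is tested only if the first is significant. Testing each visit at 2.5% gives 4.6% at ρ = 0.5.

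**The case against.** The best counter-reading is that three months simply means the 12-week visit, the only assessment at the end of that span. The remark about supports still being worn at 4 weeks can be taken as a reason not to rely on that visit. This is reasonable and may be what was intended. But the sentence speaks of a period, and the sample-size section puts 4 weeks beside 12 weeks on equal terms. If 12 weeks was meant, one sentence would settle it.

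The statistical analysis plan, which is not shown, may name the contrast. That is possible, but the point is not that detail is missing. The article states a definition, and that definition does not identify an assessment.

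Three stronger readings are tempting and should not be adopted:

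- **That the error rate is already 8–9%.** It rises only if either visit may be claimed without adjustment. The wording leaves that open; it does not announce it.
- **That the plan itself predicts disagreement between the visits.** It places the greatest benefit in the first three months, which covers both visits, and the narrowing in the longer term. Nothing says that the effect falls between 4 and 12 weeks. With 130 per arm, ρ = 0.5 and a standardised effect of 0.41 at 4 weeks, significance at 4 weeks only occurs in about 55% of trials if the 12-week effect is 0.20. It occurs in about 26% if that effect is 0.30, 15% if it is 0.35 and 6% if the effects are equal. None of these effects comes from the documents, so no frequency of disagreement can be claimed.
- **That the ambiguity gives a 20–23% chance of some false positive across the three supports.** About 12.5% arises at a single time from three comparisons with one control, which is a separate matter.

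**Conclusion.** The point stands in a conditional form. The article defines the primary time as a period containing two assessments, and no other section ranks them or combines them. If either may be claimed as primary without adjustment, the error per support-versus-Tubigrip comparison is about 8% to 9.5% instead of 5%. This rests on two-sided tests and an assumed correlation of 0.3 to 0.7. Over the wider range from 0 to 0.9 it is 9.75% to 7.0%, above 5% throughout. The chosen visit also controls which support-versus-support comparisons follow. The two visits can answer different questions because of continued device wear at 4 weeks, but how often they would disagree cannot be derived from the documents.

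**What to change.** Before unmasking, replace the defining sentence in Timing of follow-up with wording such as: *The primary time point is the 12-week assessment; 4-week and 9-month results are secondary.* Take each support-versus-Tubigrip contrast at 12 weeks, from the planned model for repeat assessments, as the primary result, and let that contrast decide which supports are compared with each other.

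If the sponsor does intend the whole period to be primary, specify instead one contrast over both visits, a fixed testing order, or an alpha split.

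In either case restate power in Sample size for the chosen contrast. For 12 weeks this needs a 12-week variance, or a plain statement that the 4-week variance is assumed to apply.

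The cost is a few sentences in the protocol and matching wording in the analysis plan, with no new outcome assessments. The article says recruitment is still under way and that follow-up data are analysed masked until the final analysis is complete, so the change can still be made blind. The downside of naming 12 weeks is that a difference at 4 weeks can be reported only as secondary.
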